##### Differences in treatment preferences between patients and clinicians

We will test the difference of the means of *b *between the patients (*b*_*p*_) and clinicians (*b*_*c*_) using an unpaired *t *test. The observed distribution of *b*_*p *_in our preliminary work was highly skewed. This was because patients clustered at the highest *b *offered. For this study, we propose to offer a maximum *b *that is twice as large as the maximum *b *offered in our preliminary study. Furthermore, we will be studying a relatively large number of patients and clinicians with distribution of the means approximating the normal distribution with SEM = SD/vn. Our sample sizes will be considerably larger than 30, a size which is often taken as a guideline threshold, above which the sample distribution of the sample mean will be reasonably normally distributed, even if the distribution of individual values is substantially skewed. Thus, the use of the t-test is appropriate. However, we will also use the Mann-Whitney test, a non-parametric test that does not require the assumption of normality of the distribution. After identifying pertinent subgroups in the analysis to Research Question 1, we will conduct modified *t *tests to test the difference of the means of *b *between the patients and the subgroup of clinicians of interest. A modified *t *test is based on the pooled estimate of variance from all the subgroups [33]. The resulting *P *values can be adjusted for multiple comparisons using the Bonferroni method (multiplying the resulting *P *value by the number of paired comparisons performed).

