Our study should be powered to determine differences in means of *b*_*p *_and *b*_*c*_, that is, differences in the treatment preferences of patients and clinicians, the key variable. In our previous study, the effect size (difference in mean *b *between patients and clinicians) was 0.9 (this is calculated from sample means (and SDs) of 2.2 (0.9) and 1.3 (0.8) in the patients and clinicians, respectively). Although it is not immediately evident what magnitude of the difference in *b *would be clinically important, readers and commentators have uniformly considered the differences we showed as important. Table 2 shows the power we would have with the proposed sample size of 96 clinicians and an equal number of patients, and also illustrates the limited impact of increasing the number of patients from 1:1 to 1:3. Therefore, given the number of clinicians available to us, we will have ≥ 80% power to detect differences in means ≥ 0.4·SD. We will have ≥ 80% power to detect differences in means of *b*_*p *_and *b*_*c *_≥ 0.75·SD between subgroups of ≥ 20 clinicians and 96 patients. In summary, after enrolling 96 patients and 96 clinicians we will have ≥ 80% power to detect (1) *b*_*p *_- *b*_*c *_> 0.4 SD, (2) odds ratio ≥ 2.6 of the proportion of patients and clinicians with *b *> *b*_*RCT *_(if that proportion is 0.63 or smaller among clinicians), and (3) a difference in mean utilities of ≥ 0.4 SD. We need to enroll 96 clinicians to ensure 8 members per focus group. Enrolling more than 96 patients has a very small impact on power. Thus, we will recruit 96 patients and 96 clinicians for this study.

**Table 2 T2:** Power to detect differences in means of *b*_*p *_and *b*_*c *_0.2 to 0.5 standard deviation units (α = 0.05)

** *Sample* **		*b*_*p *_- *b*_*c *_difference in SD units			
Clinicians	Patients	0.2	0.3	0.4	0.5
96	96	.28	.54	.79	.93
96	144	.33	.62	.86	.97
96	192	.36	.67	.89	.98
96	288	.39	,71	.92	.99

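### Table 2 contradicts both the claim of at least 80% power at 0.4 SD with 96 patients and the claim that extra patients hardly affect power

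*Protocol article*

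**What the plan says.** The Sample size estimation section of the Protocol article treats the two groups differently.

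- **Clinicians.** The number comes from the qualitative phase: "We need to enroll 96 clinicians to ensure 8 members per focus group".
- **Patients.** The number comes from a power argument. Table 2 is said to show power at the proposed sample size and "also illustrates the limited impact of increasing the number of patients from 1:1 to 1:3". The section later adds "Enrolling more than 96 patients has a very small impact on power" and concludes at once: "Thus, we will recruit 96 patients and 96 clinicians for this study".
- **Power claimed.** For the difference in mean b between the groups, "we will have ≥ 80% power to detect differences in means ≥ 0.4·SD". The closing summary repeats the 80% claim at 0.4 SD for mean b and for mean utilities.
- **Table 2.** For 96 clinicians and 96, 144, 192 or 288 patients, it gives power at differences of 0.2, 0.3, 0.4 and 0.5 SD.

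**The concern.** The only reason given for stopping at 96 patients is a statement about power, and the figures that should support it are printed beside it. At 0.4 SD they show gains that few statisticians would call very small. The planned cell is also just under the level that the text claims.

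This bears on how a null result would be read. The Discussion allows that clinicians and patients may prove to choose alike, and says this would lead to the conclusion that present anticoagulation rates are appropriate. That inference depends on which differences the design could have missed. The Sample size estimation section concedes that the clinically important size of a difference in b is not obvious, so differences below 0.4 SD cannot simply be set aside.

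**Working it through.** **Inputs.** The test of mean b is an unpaired t test (Differences in treatment preferences between patients and clinicians). From Sample size estimation: α = 0.05, 96 clinicians, 96 to 288 patients, differences of 0.2 to 0.5 SD, and prior-study means (SDs) of 2.2 (0.9) and 1.3 (0.8). Sidedness is not stated. A two-sided test reproduces Table 2, whereas a one-sided test gives 0.87 where the table has .79.

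**Step 1: reproduce the plan's figures.** With difference d in SD units and n patients, SE = √(1/96 + 1/n), and power ≈ Φ(d/SE − 1.96). At d = 0.4:

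| Patients | SE | 0.4/SE | minus 1.96 | Power, normal | Power, noncentral t | Table 2 |
|---|---|---|---|---|---|---|
| 96 | 0.1443 | 2.771 | 0.811 | 0.791 | 0.787 | .79 |
| 144 | 0.1318 | 3.036 | 1.076 | 0.859 | 0.856 | .86 |
| 192 | 0.1250 | 3.200 | 1.240 | 0.893 | 0.891 | .89 |
| 288 | 0.1179 | 3.394 | 1.434 | 0.924 | 0.923 | .92 |

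All 16 cells of Table 2 agree with calculation to within about one percentage point. The table is sound.

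**Step 2: gains over 96 patients, read from Table 2 (percentage points).**

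| Difference | Power at 96 | 144 patients | 192 patients | 288 patients |
|---|---|---|---|---|
| 0.2 SD | .28 | +5 | +8 | +11 |
| 0.3 SD | .54 | +8 | +13 | +17 |
| 0.4 SD | .79 | +7 | +10 | +13 |
| 0.5 SD | .93 | +4 | +5 | +6 |

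At 0.4 SD the type II error falls from 21% to 14%, 11% and 8%.

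**Step 3: the 80% claim.** The difference detectable with 80% power is about (1.96 + 0.84) × SE. For 96 + 96 this is 2.80 × 0.1443 = 0.404 SD. By the noncentral t it is 0.406 SD, falling to 0.371, 0.351 and 0.331 SD with 144, 192 and 288 patients. With 96 clinicians, 80% power at exactly 0.4 SD needs about 103 patients (101 by the normal approximation).

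**Step 4: the prior-study difference.** Pooled SD = √((0.9² + 0.8²)/2) = √0.725 = 0.851. The standardised difference is 0.9/0.851 = 1.06 SD. At that size, power with 96 per group is essentially 100%.

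**Step 5: what a null result could exclude.** With 96 + 96 and a common SD, the 95% confidence interval for the difference has half-width of about 1.96 × 0.1443 = 0.28 SD. To exclude a true difference of 0.4 SD, the observed difference would have to be below about 0.40 − 0.28 = 0.12 SD. A non-significant result can have an observed difference of up to about 0.28 SD, so non-significance alone does not exclude 0.4 SD.

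**The case against.** The case for the authors is substantial.

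- Table 2 is correct and printed in full, so readers can judge the description for themselves. *Limited* and *very small* are adjectives with no stated threshold.
- Returns do diminish. At 0.5 SD, tripling the patients adds only 6 points.
- At the prior-study difference of about 1.06 SD, extra patients add nothing of note. The Discussion says that substantially different choices are the likelier result.
- On the scale of b, tripling the patients lowers the detectable difference by 0.406 − 0.331 = 0.075 SD. With an SD of 0.851, that is about 0.06 units, against a prior difference of 0.9 units.

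All of this stands, and it shows that 96 patients can be defended. It does not rescue the sentences as written. The section claims its power at 0.4 SD, not at 1.06 SD. At 0.4 SD the number of patients decides whether the claimed 80% is reached.

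A reader might go further and headline the 17-point gain. That is the most favourable cell: it is at 0.3 SD, needs three times the patients, and still gives only .71. It is not the figure on which this point rests. Nor does the null-result problem arise from the 1:1 ratio alone, since power at 0.3 SD stays below 80% even with 288 patients.

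**Conclusion.** The point holds as a fault in the stated power and justification. At 0.4 SD, power with 96 + 96 is .79, not 80% or more. Extra patients would add 7 to 13 points there, so their effect is not very small. It is small only at 0.5 SD or above. This assumes a two-sided unpaired t test with a common SD, the setting that reproduces Table 2.

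A reader might infer three stronger things that the document does not support:

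- **That Table 2 is miscalculated.** It is not.
- **That the study is seriously underpowered or must enrol more patients.** The shortfall at 0.4 SD is about one point, and power is near 100% at the prior-study difference.
- **That the 1:1 ratio was really a matter of patient feasibility.** The section mentions a limit on the clinicians available but none on patients, so that reason should not be supplied for the authors.

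**What to change.** In Sample size estimation:

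1. State power at 0.4 SD with 96 + 96 as 0.79, and the difference detectable with 80% power as about 0.41 SD. Make the same correction for mean utilities, which carry the same 0.4 SD claim.
2. Replace both descriptions of the effect of more patients with the figures: at 0.4 SD, power is .79, .86, .89 and .92 with 96, 144, 192 and 288 patients.
3. Have the authors give their actual reason for 1:1. One that the document could support is that power is near 100% at the prior-study difference of about 1.06 SD.

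In the Discussion, say that a non-significant difference will be read as the groups choosing alike only if the 95% confidence interval for the difference in mean b excludes differences of concern, and state what those are. Power at 0.3 SD is only .54.

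The cost is wording. No extra patients are required and no test changes. The stated power and justification become slightly less favourable.

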## Discussion

Thousands of patients with atrial fibrillation will suffer preventable strokes this year because they do not receive anticoagulation. A number of lines of evidence, including our own prior study, suggest that differences between clinician and patient preferences regarding warfarin versus alternative management of atrial fibrillation may explain this apparent underutilization of anticoagulation. If this is so, development and testing of interventions to increase rates of anticoagulation in patients with atrial fibrillation should become a matter of urgency.

The evidence is not, however, strong enough to justify proceeding confidently with the development and testing of such interventions. In particular, we have identified methodological limitations in our prior work that raise the possibility that a different understanding of the options presented may explain differences in clinicians and patients choice. We now propose to repeat our prior study with a stronger methodology that will allow us to determine the true explanation of the results. We may find that, when they understand the options in a similar way, clinicians and patients make similar choices. If this proves to be the case, it would suggest that the low rates of anticoagulation in patients with atrial fibrillation reflect a shared aversion to bleeding risk in clinicians and patients. Such a finding would prompt the conclusion that current rates of anticoagulation are, in fact, appropriate.

Our review of the evidence suggests that it is more likely that we will confirm substantially different treatment choices in clinicians and patients. This result would suggest that current low rates of anticoagulation in atrial fibrillation reflect clinician and not patient values, and mandate urgent development and testing of interventions to increase rates of anticoagulation, and thus prevent unnecessary strokes. Such findings would not, however, explain why clinician and patient choices differ. We see two leading possibilities. One is that, relative to patients, clinicians experience the post-stroke state as relatively less aversive, and having a gastrointestinal bleed as relatively more aversive, than do patients. The second explanation is that clinicians and patients share the same values for stroke and bleeding, but the circumstances of clinical decision-making lead clinicians to make different choices. In particular, we hypothesize that omission bias associated with efforts to reduce clinician-generated risk, may explain the results. This explanation posits that clinicians put more weight on commission of a behavior that leads to adverse consequences (bleeding through warfarin administration) than an omission of behavior that could lead to beneficial consequences (stroke prevention through warfarin administration). We will explore this issue through direct measurement of utilities for stroke and bleeding, and through focus groups with the participating clinicians.

On completion of this study, we will hope to achieve major advances in understanding clinician and patient decision-making in atrial fibrillation. Our anticipated results will challenge investigators, medical educators, and health care providers to develop and test strategies to deal with differences in clinician and patient choices. Our results will guide the development of these strategies, which may include innovations in undergraduate and post-graduate education, enhancements to the clinical encounter to facilitate patient-clinician communication and shared decision-making, increasing use of decision support tools in clinical practice, and monitoring and feedback of clinician success in providing optimal anticoagulation in patients with atrial fibrillation. For example, our experience using decision boards in this study will inform the organization and conduct of a randomized controlled trial to test their efficacy in helping patients with atrial fibrillation make informed choices.

## Abbreviations

AF: atrial fibrillation; EC: extracranial; N: sample size; SD: standard deviation; SEM: Standard error of the mean.
